### Quality control, data management and monitoring

Prior to recruitment, research team members will be required to attend a training workshop to ensure their strict adherence to the research protocol, and that they have a comprehensive understanding of the trial management process. The intervention will be implemented by attending physicians with at least 3 years of hospital experience. The trial process will be conducted in accordance with a researcher’s manual of standard operating procedures developed in consultation with experts with extensive therapeutic experience. To improve compliance, we maintained contact with the subjects and at least one family member of the subjects, and regular telephone follow-up was conducted.

This data will be collected and recorded on CRF. All data will be input to a password-protected computer by a staff member who does not know how the group assignments were made. It will be checked twice by investigators after the data is entered. The collected clinical data will be entered into the database and the database will be regularly updated according to follow-up timing. The original CRF and all database data will be securely stored in the Oncology Department building at Zhongshan Hospital of Traditional Chinese Medicine affiliated to Guangzhou University of Chinese Medicine. Throughout the trial, two trained, qualified, and independent supervisors will regularly visit the trial center to be responsible for data monitoring, regulatory management, and to conduct a trial audit every 3 months, independent of the investigator and the organizer. This will include specification of the random inspection program, the reasonableness of the inclusion and exclusion criteria, the proper implementation, the implementation of informed consent procedures, the specification of the CRF, the confidential updating of the database, and SAE reporting, and also determining whether to terminate the study prematurely. For any cases in which there is shedding or loss of visit, it will be necessary to explain the reasons for the shedding and the loss of visit, and calculate the proportion of cases in which there was shedding and loss of visit relative to the total number of observed cases.

### Sample size calculation

The sample size estimation was conducted using the Logrank Test, with disease-free survival (DFS) as the primary outcome measure. According to the JCOG0603 study, patients with mCRC who achieved NED status and received adjuvant chemotherapy had a 3-year DFS rate of 52.1% [7]. Based on the data from the phase II single-arm CAMCO trial [21], in conjunction with clinical expertise and expert opinions, We hypothesized that the 3-year DFS rate in the group receiving capecitabine metronomic chemotherapy would be 67.1%. We will need at least 119 participants in the intervention and control group, 238 participants in total (alpha = 0.05, power=0.90,). A drop-out of 5% is anticipated [22]. The sample size of this study was determined to be 240 participants, taking into account potential additional dropouts.

We calculated the sample size using the Lakatos method, which accounts for varying accrual times, dropout rates, and study length—critical factors for trials with survival endpoints like DFS. While the Freedman method is widely used for its simplicity, it assumes constant hazard ratios and patient compliance, which may not fully reflect the complexities of real-world trials. The Lakatos method [23], though more restrictive in its assumptions, offers a more realistic model for time-dependent variables and survival data, making it a better fit for our single-center study [24].

However, some assumptions of the Lakatos method may not hold in practice, potentially resulting in a wider confidence interval (CI) for the hazard ratio (HR). Although the Lakatos method may yield a smaller sample size compared to Freedman’s, we have carefully balanced statistical rigor with the feasibility of a single-center trial, given our available resources. To mitigate the risk of wide CIs, we will closely monitor accrual patterns and dropout rates throughout the study to ensure robust results.

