### Intervention

The interventions studied will be implemented by attending physicians with at least 3 years of clinical experience in the Oncology Department at Zhongshan Affiliated Hospital, Guangzhou University of Chinese Medicine. Based on chemotherapy theory for metastatic colorectal cancer and previous randomized controlled trials, capecitabine chemotherapy process interventions will be developed under the consensus of colorectal cancer oncology experts. Prior to initiating the study, the clinical practitioner will receive specialized training to gain a comprehensive understanding of capecitabine metronomic chemotherapy, and to administer treatment in accordance with the specific requirements of the investigator’s manual. All eligible patients in both groups will have been diagnosed with stage IV colon cancer with hepatic and/or lung metastases, have potentially cured R0 resection of the primary tumor and metastatic lesion (including local treatments such as radiofrequency ablation), have completed perioperative chemotherapy, and have reached NED status on computed tomography (CT) or MRI within 4 weeks of enrollment. The study will be conducted over a 3-year period, with all treatments completed within the first 2 years. Follow-up will last for 12 months, beginning after the completion of the 24-month intervention period.

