### Statistical analysis

The statistical analysis will use SPSS version 26.0 (IBM SPSS Statistics, New York, USA). All analysis will be based on the ITT dataset. Missing data will be supplemented with the principle of multiple interpolation. All statistical tests will use a two-side test, and *P* < 0.05 will be considered statistically significant for the difference being tested. The survival analysis will use the Kaplan-Meier method for one-factor survival, calculating the median disease DFS and OS of the two groups, and comparing the survival curves by the Logrank test. The χ² test will be used to analyze the counting data of adverse events (AEs). Additionally, the 95% confidence interval (CI) for the observed hazard ratio (HR) will be calculated at the end of the trial. *P* <0.05 will be considered statistically significant.

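### The stated 90% power for 238 patients does not follow from the protocol's own inputs: under proportional hazards it is about 67% at 36 months each, and about 52% to 76% across accrual patterns within the stated calendar

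*Protocol article*

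**What the plan says.** The Sample size calculation section describes a log-rank calculation on the primary endpoint: "The sample size estimation was conducted using the Logrank Test, with disease-free survival (DFS) as the primary outcome measure". The control rate comes from a cited trial whose patients "had a 3-year DFS rate of 52.1" (per cent). For the experimental arm, "We hypothesized that the 3-year DFS rate in the group receiving capecitabine metronomic chemotherapy would be 67.1" (per cent). The result is "We will need at least 119 participants in the intervention and control group, 238 participants in total (alpha = 0.05, power=0.90". The total is then set at 240, with 5% drop-out anticipated.

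The section names the Lakatos method as the one used and says of it: "Although the Lakatos method may yield a smaller sample size compared to Freedman’s". It gives no hazard ratio, event number, accrual period or hazard shape.

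Three other places fix inputs:
- Statistical analysis: "All statistical tests will use a two-side test".
- Intervention: "The study will be conducted over a 3-year period, with all treatments completed within the first 2 years", with 12 months of follow-up after the 24-month intervention period, so 36 months per patient.
- Study subjects and Trial status: the trial runs from December 2021 to December 2025.

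**The concern.** For a log-rank test, power depends on the number of events and the hazard ratio. A 15-point difference at three years, with about 40% of patients having an event, looks too small for 238 patients to give 90% power. The article prints a specific power figure next to the inputs needed to check it, so this is not a detail left to an analysis plan.

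If power is nearer two thirds, the trial would miss the hypothesised benefit about one time in three, rather than one in ten. A non-significant result reported against a 90% claim could be given more weight as evidence of no effect than it deserves.

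**Working it through.** **Inputs.** 3-year DFS 52.1% and 67.1%, alpha 0.05, power 0.90, N = 238, 5% drop-out (Sample size calculation); two-sided tests (Statistical analysis); 1:1 allocation (Randomization, allocation and blinding); 36 months per patient (Intervention). Added assumption: proportional hazards.

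**Hazard ratio.** HR = ln(0.671)/ln(0.521) = (−0.3990)/(−0.6520) = 0.612, so ln HR = −0.491.

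**Trying to reproduce 238.** With z-values 1.960 + 1.2816 = 3.2415, squared 10.507:
- Schoenfeld: events = 4 × 10.507 / 0.491² = 174.2.
- Freedman: events = 10.507 × [(1 + 0.612)/(1 − 0.612)]² = 181.3.
- Mean probability of an event within 36 months = (0.479 + 0.329)/2 = 0.404.
- N = 174.2/0.404 = 431, or 181.3/0.404 = 449. Rounding up at each step gives 434 and 451.
- A comparison of two proportions at three years needs 223 per arm, 446 in total.

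The stated 238 is not reproduced. A one-sided 5% test, which would contradict the Statistical analysis section, still needs 142 events and 352 patients. A figure close to 238 appeared only with inputs the article does not state, for example 235 with one-sided 80% power, 1-year accrual, 3 further years of follow-up and 5% drop-out.

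**Power of the stated sample.** Power = Φ(√events / 2 × 0.491 − 1.960).
- 238 patients: 238 × 0.404 = 96.2 events; Φ(2.408 − 1.960) = 67.3%.
- 240 patients: 97.0 events; Φ(2.418 − 1.960) = 67.7%.
- 228 patients (240 × 0.95, counting lost patients as contributing nothing): 92.1 events; Φ(2.357 − 1.960) = 65.4%.
- A simulated log-rank test (4,000 runs, constant hazards) gave 66% with 119 per arm and 90% with 216 per arm.

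**Accrual not stated.** Taking constant hazards of −ln(0.521)/3 = 0.217 and −ln(0.671)/3 = 0.133 per year, uniform accrual, and everyone followed to the end of a four-year calendar:

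| Accrual | Mean event probability | Power, N = 238, two-sided |
|---|---|---|
| all at the start | 0.497 | 76% |
| 1 year | 0.452 | 72% |
| 2 years | 0.401 | 67% |
| 3 years | 0.343 | 60% |
| 4 years | 0.278 | 52% |

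Outside that calendar, 4 years of accrual plus 3 more years for everyone gives 81%.

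**Lakatos.** The Lakatos interval-by-interval calculation, with constant hazards over 36 months, gives N of about 438 and about 67% power at 238. Adding 5% drop-out over three years raises N to about 449 and lowers power to about 66%.

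**Effect detectable with 90% power.** With 240 patients at 36 months, HR 0.507 means a 3-year DFS of 0.521^0.507 = 71.9%. Events = 240 × (0.479 + 0.281)/2 = about 91, and power is 90%.

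**The case against.** The strongest reply is that the article claims no constant hazards and chose Lakatos precisely to allow time-dependent effects, so inputs not shown might support 238. It is true that the hazard shape is unstated and that proportional hazards is an assumption of this check. The shape does move the figure. Keeping both 3-year rates and a constant control hazard, an effect confined to the two treatment years gives about 75% power (N about 357), and an effect starting only after one year gives about 57% (N about 554). Neither approaches 90%. Drop-out works against the claim.

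It can also be said that the article is candid. It concedes that the confidence interval may be wide, lists the small single-centre sample as a limitation, and commits to reporting a 95% interval for the hazard ratio. That lowers the risk of misreading a null result, but does not correct the power figure.

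Three stronger readings are tempting, and the documents do not support them:
- That power is 67% and nothing else. This is the case of 36 months for everyone with proportional hazards. A patient enrolled after December 2022 cannot complete 36 months by December 2025, and the accrual period is not given, so a range is needed.
- That 240 patients have 90% power at HR 0.52. This keeps 97 events, the count expected at HR 0.61. At HR 0.52 the expected count is 240 × (0.479 + 0.288)/2 = about 92, and power is about 88%.
- That the trial must enrol about 431 patients. The error lies in the stated power, and restating it is enough.

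**Conclusion.** The printed power is wrong for the printed inputs. Under proportional hazards, 238 patients followed for 36 months give about 96 DFS events and about 67% power at two-sided 5%. Reaching 90% would take about 174 to 181 events and 431 to 449 patients. With accrual unstated, power within the four-year calendar is about 52% to 76%. One-sided testing (78% at 36 months) and the choice of Lakatos over Freedman do not account for the difference, nor does either of the two delayed or waning effects tried. The exact figure depends on the assumed hazard shape and accrual; the conclusion that it is well below 90% does not. The claim should be corrected before results are read against it.

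**What to change.** Replace the power statement in the Sample size calculation section. For example:

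> 240 patients followed for 36 months are expected to give about 97 DFS events and about 68% power (about 65% after 5% loss) for a hazard ratio of 0.61 with a two-sided 5% log-rank test, assuming proportional hazards. 90% power is reached only for a hazard ratio of about 0.51 (3-year DFS about 72%, about 91 events).

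State the hazard ratio, the expected number of events, and the accrual period and follow-up used. If 36 months cannot be completed for everyone by December 2025, give the power for the accrual pattern that applies. Remove the suggestion that the Lakatos method justifies a smaller sample.

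The cost is a rewritten section and a less favourable power figure; no extra patients are needed. Continuing follow-up to a target event count is a separate and larger decision. It would run past the planned 12 months of follow-up and the December 2025 end, and 174 events from 238 patients would take about 7.8 years of follow-up each.

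### Monitoring accrual and drop-out is not a sufficient safeguard against a wide hazard-ratio interval, because the DFS event count that sets its width is neither stated nor monitored

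*Protocol article*

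**What the plan says.** The Sample size calculation section rests the design on DFS. It takes from an earlier trial that "patients with mCRC who achieved NED status and received adjuvant chemotherapy had a 3-year DFS rate of 52.1"% and supposes that "the 3-year DFS rate in the group receiving capecitabine metronomic chemotherapy would be 67.1"%. It then states: "We will need at least 119 participants in the intervention and control group, 238 participants in total (alpha = 0.05, power=0.90"). The total is set at 240 with 5% drop-out anticipated. No number of DFS events is given.

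The section goes on to concede that assumptions of the sample-size method may fail and widen the interval for the HR. Its remedy is: "To mitigate the risk of wide CIs, we will closely monitor accrual patterns and dropout rates throughout the study to ensure robust results".

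Three other places bear on the point:
- Statistical analysis: "the 95% confidence interval (CI) for the observed hazard ratio (HR) will be calculated at the end of the trial", and "All statistical tests will use a two-side test".
- Intervention: "Follow-up will last for 12 months, beginning after the completion of the 24-month intervention period", which makes 36 months per patient. The two group descriptions say the same. Study subjects and Trial status, however, end the trial in December 2025, four years after its start, and Trial status says that recruitment is still open.
- Quality control, data management and monitoring: "the database will be regularly updated according to follow-up timing". Primary outcomes sets DFS assessment every 3 months.

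**The concern.** The sentence makes a positive claim: that watching two quantities will protect the precision of the primary estimate. That can be judged on its own terms. For a log-rank or Cox comparison with equal arms, the standard error of the log HR is close to 2 divided by the square root of the number of events. Accrual and drop-out affect precision only by changing that number. A third input, the underlying DFS event rate, changes it as well and is not in the sentence. Both monitored quantities could therefore run exactly to plan while the trial holds too few events. The assurance also follows directly on a stated power of 0.90, so a reader will take it that good accrual and low drop-out deliver the precision that goes with that power.

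**Working it through.** **Inputs from the article.** 3-year DFS 52.1% and 67.1%; two-sided alpha 0.05; power 0.90; 119 per arm (238), set to 240; drop-out 5%; 24 + 12 = 36 months per patient; calendar window 31 December 2021 to 31 December 2025 (48 months).

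**Assumptions.** Exponential DFS, proportional hazards, non-informative exponential drop-out stated as a 3-year cumulative figure (the article gives no period), and uniform accrual where accrual is varied.

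**1. The plan's own figure.** HR = ln 0.671 / ln 0.521 = 0.612. Events needed = 4(1.960 + 1.282)² / (ln 0.612)² = 175 (Schoenfeld); Freedman's formula gives 182. The average 36-month event probability is 1 − (0.521 + 0.671)/2 = 0.404. Patients needed: 175/0.404 ≈ 433, or 182/0.404 ≈ 450. The stated 238 is not reproduced. To yield 175 events, 238 patients would need an event probability of 175/238 = 0.735, or about 96 months of follow-up each.

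**2. Events if both monitored quantities are perfect.** 120 × (0.479 + 0.329) = 97.0. Interval factor = exp(1.96 × 2/√97) = 1.489, so the expected CI is 0.612/1.489 to 0.612 × 1.489 = 0.41 to 0.91. Power = Φ(0.491 × √97/2 − 1.96) ≈ 0.68. At 175 events the factor is 1.345 and the CI 0.46 to 0.82.

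**3. What moves the interval.** Events per arm = n·h/(h+d)·(1 − exp(−36(h+d))), with h = −ln(S₃)/36 and d = −ln(1 − drop-out)/36. HR is held at 0.612.

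| Scenario | Events | Expected 95% CI | Upper/lower |
|---|---|---|---|
| 240 patients, 36 months, no drop-out | 97 | 0.41–0.91 | 2.22 |
| same, 5% drop-out | 95 | 0.41–0.92 | 2.24 |
| same, 20% drop-out | 88 | 0.40–0.93 | 2.31 |
| control DFS 62%, no drop-out | 76 | 0.39–0.96 | 2.46 |
| control DFS 67%, no drop-out | 66 | 0.38–0.99 | 2.63 |
| 200 enrolled, 5% drop-out | 79 | 0.39–0.95 | 2.42 |
| 160 enrolled, 5% drop-out | 63 | 0.37–1.00 | 2.68 |

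**4. Data cut at 31 December 2025.** A patient randomised after December 2022 cannot complete 36 months by that date. With 240 patients, 5% drop-out and follow-up capped at 36 months:

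| Uniform accrual over | Events | Upper limit | Upper/lower | Power |
|---|---|---|---|---|
| 12 months | 95 | 0.92 | 2.24 | 0.67 |
| 24 months | 89 | 0.93 | 2.30 | 0.64 |
| 36 months | 77 | 0.96 | 2.44 | 0.58 |
| 48 months | 63 | 1.00 | 2.69 | 0.49 |

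Raising drop-out from 5% to 20% adds 0.07 to the upper/lower ratio. Raising control DFS by 10 to 15 points adds 0.24 to 0.41. Slow accrual under the calendar cut adds up to 0.45.

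**The case against.** A reader might infer that the safeguard cannot work at all, because under a fixed 36 months per patient the timing of accrual leaves the interval unchanged and drop-out moves it little. The documents do not support that. Even with fixed follow-up, a shortfall in total enrolment is costly (160 patients give about 63 events), and recruitment is the obvious risk at a single centre. Under the stated end date, the accrual pattern is itself a main driver of width. Monitoring accrual and drop-out can therefore limit further loss. The section also ties the wide-interval risk to a method whose named inputs are accrual times, drop-out and study length, so the monitors match two of those three. This stands, and it limits the point to insufficiency.

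A reader might also infer that an event shortfall would stay hidden until the end. The article does not show that: DFS is assessed every 3 months, the database is updated, independent supervisors audit every 3 months, and a fuller protocol or SAP may hold event-tracking rules. What can be said is narrower: neither quantity named in the remedy would reveal a low event rate.

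Finally, the article admits uncertainty from its small sample and states no numerical precision, so no figure for the interval is wrong. The assurance of robust results is loose wording. It is still unsupported at the article's own rates.

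**Conclusion.** The point holds as one of insufficiency. The only named remedy omits the quantity that determines the interval, and perfect performance on both monitored quantities still leaves about 97 events, CI about 0.41 to 0.91 and power about 0.68, against about 175 events and CI about 0.46 to 0.82 for the stated 0.90. A plausible miss in the event rate (76 to 66 events) would not appear in either monitor. Accrual effects are real (95 down to 63 events under the calendar cut), but they too are read most directly from the event count.

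It would be a mistake to take about 97 events as an adequate target. It is only what 240 patients are projected to yield. The gap to 175 is a separate and larger sample-size problem, which better monitoring does not cure. The figures rest on the assumptions listed with the calculations; other hazard shapes would shift the counts.

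**What to change.** 1. Replace the closing assurance in the Sample size calculation section with the expected event count and interval at the design rates: about 95 to 97 DFS events and a 95% CI of about 0.41 to 0.91. Say plainly that this is below the roughly 175 events that the stated power needs, so the figure is a projection and not a sufficient target.
2. Keep the monitoring of accrual and drop-out, and add a count of DFS events pooled over both arms, never split by arm, at each 3-monthly database update, compared with the number projected from actual enrolment dates.
3. Reconcile the 36 months of follow-up per patient (Intervention and the two group descriptions) with the December 2025 end date (Study subjects, Trial status). Prespecify that, if pooled events are short, the primary DFS cut-off is deferred to a common later date, up to a stated latest date.

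Cost: a short protocol amendment. The count uses data already collected, keeps assessors and analysts blinded, and spends no alpha. Counting alone narrows nothing, so the deferral rule is the working part. Its downside is that the closing date may move, and events arising after treatment has ended may dilute the HR.

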### Statistical analysis

The statistical analysis will use SPSS version 26.0 (IBM SPSS Statistics, New York, USA). All analysis will be based on the ITT dataset. Missing data will be supplemented with the principle of multiple interpolation. All statistical tests will use a two-side test, and *P* < 0.05 will be considered statistically significant for the difference being tested. The survival analysis will use the Kaplan-Meier method for one-factor survival, calculating the median disease DFS and OS of the two groups, and comparing the survival curves by the Logrank test. The χ² test will be used to analyze the counting data of adverse events (AEs). Additionally, the 95% confidence interval (CI) for the observed hazard ratio (HR) will be calculated at the end of the trial. *P* <0.05 will be considered statistically significant.

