### Randomization, allocation and blinding

Eligible patients will be randomly assigned to either a watch-and-wait group or a capecitabine metronomic chemotherapy group in equal proportions via the random number table method. After the participants sign the informed consent form and complete the baseline assessment, the investigators will assign them a random number and assign the participants to the appropriate group. Participants will be informed that they have an equal chance of being assigned to the capecitabine metronomic chemotherapy group or to the watch-and-wait group. Subject assignment will be performed by an independent investigator in the clinical department who will not be involved in the evaluation of the results. The outcome assessors, data collectors, and statisticians will be blinded to the intervention assignment, but the patients participating in the study will not be blinded. Single blinding of the outcome assessors and data analysts will be maintained throughout the course of the study.The overall study design is illustrated in Fig 2.

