#### Capecitabine metronomic chemotherapy group.

All eligible patients will have been diagnosed with Stage IV mCRC according to the National Cancer Network (NCCN) colorectal cancer diagnosis and treatment guidelines. They also will have achieved NED after local treatment such as surgery or ablation and completed perioperative 6-month chemotherapy.

In the capecitabine metronomic chemotherapy group, after chemotherapy ends, patients will continue to take capecitabine (500 mg/m^2^ bid, uninterrupted) for 2 years, or until the disease progresses or the patient develops intolerable side effects. Retrieve the medication box and conduct a count of the remaining quantity to assess adherence, including instances of underdosing, overdosing, or loss of medication. During the trial period, each observation index will be re-visited every 3 months from postoperative intervals to determine whether there is any recurrent metastasis of the tumor. The follow-up will last for 1 year, and the observation indicators will be re-visited every 3 months.

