## Outcome

The primary endpoints disease-free survival (DFS) will be analyzed by using intention-to-treat (ITT) data set from randomization, stratified by preoperative chemotherapy, metastatic organs, number of metastases, lenght of previous systemic treatment (under 6 months, over 6 months), response to previous chemo: CR/PR or SD/PD. Secondary endpoints will include overall survival (OS), 1-year, 2- year and 3-year survival rate. The adverse reactions will be counted, and the bone marrow suppression rate and the incidence of digestive tract reactions will be used as safety evaluations.

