#### Safety.

All participants will undergo physical tests to evaluate their bodies before screening enrolling and after treatment. These tests will include the function of the heart, liver, kidneys, and other organs, including cardiac ultrasound, ECG, white blood cell count, hematocrit, platelets, aspartate aminotransferase/alanine transaminase, blood urea nitrogen, creatinine, γ-glutamyl transpeptidase, and erythrocyte sedimentation rate.

Adverse events (AEs) are any unexpected adverse conditions, symptoms, or sensations that occur in subjects throughout the trial period, whether or not they are associated with capecitabine treatment. AE will be graded using the Common Terminology Standard (CTCAE) 4.0.3 [20]. A serious adverse event (SAE) will be defined as any of grade 3, 4, or 5 adverse events. Each AE will be recorded on the case report form (CRF). SAE will be reported to the Competent Authorities and the Ethics Committee. Initiators must submit annual safety reports to Competent Authorities and Ethics Committees during clinical trials. At the same time, the incidence of bone marrow suppression and the incidence of gastrointestinal responses will be counted to assess the safety of capecitabine metronomic chemotherapy.

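### The ITT rule covers every analysis, adverse events included, so capecitabine patients who never take a dose stay in the toxicity denominator (minor)

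*Protocol article*

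**What the plan says.** The Statistical analysis section sets one population for everything: "All analysis will be based on the ITT dataset". The same paragraph goes on to the survival methods and a chi-square test for adverse event counts, with no exception for safety.

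The Outcome section is narrower. There it is the primary endpoint, DFS, that "will be analyzed by using intention-to-treat (ITT) data set from randomization". For safety it says only that "the bone marrow suppression rate and the incidence of digestive tract reactions will be used as safety evaluations", without a denominator. The Safety section gives the purpose of those rates: "the incidence of bone marrow suppression and the incidence of gastrointestinal responses will be counted to assess the safety of capecitabine metronomic chemotherapy".

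Three other places bear on the point:

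- Randomization, allocation and blinding: the random number is assigned after consent and baseline assessment, and "the patients participating in the study will not be blinded".
- Capecitabine metronomic chemotherapy group: staff retrieve the medication box and "conduct a count of the remaining quantity to assess adherence, including instances of underdosing, overdosing, or loss of medication".
- Table 1: patients with poor compliance, known DPD deficiency or capecitabine intolerance are excluded.

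**The concern.** The safety rates are there to describe what the drug does to people who take it. A patient who is randomised to capecitabine, learns the allocation and declines before the first dose gives no information on its toxicity. Under the rule as written, that patient still counts in the capecitabine denominator, usually as someone without the event.

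Such a refusal is possible. Patients know their arm, and the regimen is two more years of daily oral chemotherapy after six months of perioperative chemotherapy. The exclusions in Table 1 make it less likely but cannot rule it out. Patients who start and then stop are not affected, because they belong in the safety denominator either way.

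If capecitabine raises these rates, the dilution leans toward a finding of good tolerability. Low toxicity is a main part of the trial's rationale, so the lean favours the hypothesis. Safety is also one of the trial's stated aims, alongside efficacy.

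**Working it through.** The article gives no adverse event rate and no non-start rate, so there is no figure of its own to reproduce. The check is how far the rule could move the result.

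**Inputs**

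- n = 120 per arm (Study design).
- f = share of the capecitabine arm that never takes a dose. Not given; assumed 0, 3/120 and 6/120. The last borrows from Sample size calculation, "A drop-out of 5% is anticipated": 0.05 × 120 = 6. That figure is for drop-out and is not a non-start rate.
- a = adverse event risk among treated patients, b = risk off drug. Not given; assumed pairs below.
- Non-starters are first given the off-drug risk b.

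**Formulas**

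- Capecitabine-arm rate under ITT = a(1 − f) + bf
- Difference from control = (a − b)(1 − f)
- Loss = (a − b)f
- 95% half-width at f = 0: 1.96 × √[a(1 − a)/120 + b(1 − b)/120]

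**Main scenario, a = 30%, b = 10%**

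| Non-starters | Capecitabine-arm rate | Difference | Loss |
|---|---|---|---|
| 0 | 30.0% | 20.0 points | 0 |
| 3 | 29.5% | 19.5 points | 0.5 point |
| 6 | 29.0% | 19.0 points | 1.0 point |

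Standard error at f = 0: √(0.21/120 + 0.09/120) = 0.050, so the half-width is 1.96 × 0.050 = 9.8 points. The largest loss is 1.0/9.8, about a tenth of that.

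**Other assumed risks, 6 non-starters**

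| a vs b | Loss | 95% half-width |
|---|---|---|
| 15% vs 5% | 0.5 point | 7.5 points |
| 50% vs 20% | 1.5 points | 11.5 points |

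**Relaxing the assumption on non-starters.** If their own risk is c, the loss in the capecitabine-arm rate is (a − c)f. At a = 30% and f = 5%, c = 0 gives 1.5 points, c = 10% gives 1.0, c = 20% gives 0.5, and c = 30% gives none. The rate is diluted whenever c is below a.

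**Effect on the test.** At 20% vs 5% with 6 non-starters, the ITT capecitabine-arm rate is 0.95 × 20% + 0.05 × 5% = 19.25%. Power of the two-sided 5% comparison is 0.927 under ITT and 0.940 on a set of 114 treated patients against 120 controls.

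**Precision after the change.** At 30% vs 10% with 6 non-starters:

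- ITT (rate 29%, n = 120): 1.96 × √(0.2059/120 + 0.09/120) = 9.7 points.
- Treated patients only (rate 30%, n = 114): 1.96 × √(0.21/114 + 0.09/120) = 10.0 points.

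**The case against.** The strongest reply is that the effect is too small to matter. Even the main scenario counts all of the anticipated drop-out as patients who never started, which is generous given the exclusions in Table 1 and a consent process that explains the equal chance of either arm. With 1 or 2 non-starters at 30% vs 10%, the loss is 0.20 × 1/120 = 0.17 point or 0.20 × 2/120 = 0.33 point. No tolerability threshold is set that such a shift could cross. All of this stands, and it is why the point is minor.

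A second reply is that an as-randomised comparison of adverse events is legitimate. The Safety section counts events over the whole trial period whether or not they are related to capecitabine, and dropping non-starters removes patients from one arm only. Patients who decline may also carry residual toxicity from earlier chemotherapy, so their risk could exceed the off-drug average, and excluding them could leave a group that tolerates treatment better. This qualifies the direction and size, as the calculation with c shows, and it is a good reason to keep the as-randomised table. It does not make that table the best main answer to a question about the drug's safety.

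A third reply is that a journal article may leave the definition of a safety set to the full protocol or analysis plan. That would answer silence. Here the article states a rule for all analyses, and a safety set defined elsewhere would contradict the published sentence.

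**Conclusion.** The point holds and is minor. The article extends ITT to adverse events by a positive statement, and that fits its own safety aim poorly. Under the assumed risks, with up to 6 of 120 non-starters carrying the off-drug risk, the loss is 0.5 to 1.5 points against half-widths of 7.5 to 11.5 points. If every patient starts, it is zero. The rule can dilute harm; nothing in the document shows that it will. The direction, toward better tolerability, requires that capecitabine raises these rates and that non-starters' risk is below that of treated patients. DFS, OS and the sample size are not affected.

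**What to change.** Replace the sentence with two: *DFS and OS will be analysed on the ITT dataset. Adverse events, bone marrow suppression and digestive tract reactions will be analysed on a safety set.*

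Define the safety set as follows:

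- Capecitabine group: patients randomised to capecitabine who took at least one dose, established from dosing records with the medication box counts as a check. A lost or empty box does not prove a dose was taken, so exclude only documented non-starters and keep unclear cases in.
- Comparator: the watch-and-wait arm as randomised.
- Adverse event collection and the observation period: unchanged from the Safety section, for both arms.
- Sensitivity analysis: the adverse event table as randomised.

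The cost is two sentences, a first-dose entry on the case report form if there is none, and one extra table. The main safety comparison is then no longer strictly as randomised, which the sensitivity table covers, and precision barely changes. The article reports that the trial was still recruiting, so the set can be fixed before anyone chooses a denominator knowing who did not start.
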